**Figure 2 fig2:**
[figure not shown]
Acupoints of Baihui (Du 21) and Dazhui (Du 14).

**Figure 3 fig3:**
[figure not shown]
Acupoints of temporal three-needle.

### Outcome measurement

Clinical indicators will be conducted uniformly by professional physicians or therapists. NIHSS scores will be assessed once before treatment (Day 1), during treatment (Day 5), and after treatment (Day 10). BMI and mRS scores will be assessed before treatment (Day 1) and after treatment (Day 10).

## Main results

The National Institutes of Health Stroke Scale (NIHSS) (19, 20), consists of 11 assessment items: degree of consciousness, ability to answer questions, ability to follow instructions, eye movements, visual fields, facial muscle strength, upper and lower extremity motor function, limb coordination, sensory functioning, speech, phonology, and sensory neglect. Each item is scored on a scale of 0 to 4, resulting in a total score ranging from 0 to 42, with higher scores indicating more severe neurological damage. Scores of 0–1 indicate normal or near-normal status; 2–4 indicate mild stroke; 5–15 indicate moderate stroke; 15–20 indicate moderate to severe stroke; and scores of 20 or more indicate severe stroke, with higher scores reflecting more severe conditions. To ensure the reliability and consistency of the NIHSS scoring, all assessors will undergo standardized training. The training will cover a detailed explanation of the scoring criteria, common scoring errors, and methods to avoid bias. The process will ensure that assessors fully understand the meaning of each scoring item and can accurately apply it during the actual assessment. After the training, assessors will be tested through both written exams and practical scoring to verify their proficiency. Additionally, the results of consistency tests, including the Kappa value (which reflects the strength of consistency, with values typically >0.75 indicating strong consistency), will be provided to evaluate the inter-rater reliability of the scoring.

### Secondary results

Activities of Daily Living: Modified Barthel Index (MBI); The Modified Barthel Index (MBI) (21, 22) is used to assess a patient’s functional status in activities of daily living (ADLs), with individual scores based on a series of independent behavioral measurements and a total score ranging from 0 to 100. The Barthel Index developed in 1965 by American researchers Dorothea Barthel and Florence Mahoney, is a widely used tool for assessing ADLs in rehabilitation settings, particularly in the United States. Barthel Index Assessment Criteria:

60 points or more: Mildly disabled, but essentially independently.40 to 60 points: Moderately disabled, requiring assistance with daily activities.20 to 40 points: Severely disabled, requiring significant assistance with daily activities.Less than 20 points: Totally disabled, completely dependence.

Assessment of Disability: The Modified Rankin Scale (mRS) (23, 24) is used to assess neurological recovery in stroke patients. mRS Scoring Criteria:

0 points: Asymptomatic; mild symptoms may be present, but the patient has not experienced any new functional limitations after the stroke.1 point: Symptoms are present, but there is no significant disability; the patient can complete all regular responsibilities and activities.2 points: Mild disability; the patient cannot perform all previously completed activities but can manage personal affairs independently.3 points: Moderate disability; the patient requires some assistance but can walk independently.4 points: Severe disability; the patient is unable to walk without assistance and cannot attend to their own physical needs.5 points: Severe disability; the patient is bedridden and incontinent, requiring constant care and attention. Although a trained nurse is not necessary, the patient needs someone to assist them several times throughout the day and night.

### Blood serum index

In this study, enzyme-linked immunosorbent assay (ELISA) will quantify patients’ expression of inflammatory factors, including TNF-*α* and IL-1β (25), vascular endothelial growth factor (VEGF) (26), endothelial repressor ES (27),and peripheral blood mononuclear cells at pre-trial (Day 1), on-treatment (Day 5), and post-treatment (Day 10) levels. Additionally, flow cytometry will measure the CD14+ and CD14- levels of mononuclear cells in peripheral blood (28).

### Safety outcomes

The researchers will closely monitor patients during treatment, recording vital signs such as temperature, respiratory rate, pulse rate, and blood pressure. If the patient experiences any discomfort, the intervention will be stopped immediately, and appropriate treatment will be provided based on the patient’s condition. Any adverse reactions from needling, including localized redness, swelling, pain, or other events, will be documented by the operator. The study will now employ the internationally recognized Common Terminology Criteria for Adverse Events (CTCAE) to categorize and grade the severity of adverse events.

### Follow-up

Patients will be followed up at 1 and 3 months post-discharge, with assessments of daily living ability (using the MBI scale) and disability (using the mRS scale).

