### Study design

This is a randomized controlled trial with evaluator blinding to be conducted at the First Affiliated Hospital of Guangzhou University of Chinese Medicine. A total of 66 emergency inpatients will participate in this study. The experimental flowchart is shown in Figure 1. This study has received approval from the Ethics Committee of the First Affiliated Hospital of Guangzhou University of Traditional Chinese Medicine (Ethics Acceptance Number: JY2024-116).

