### Inclusion criteria

(1) Meets the diagnostic criteria for acute cerebral infarction as outlined in the “Guidelines for the Prevention and Treatment of Stroke in China” (2021 edition), and diagnosed through head CT or MRI examination;(2) Meets the diagnostic criteria for stroke as defined by Traditional Chinese Medicine (TCM);(3) Individuals experiencing their first stroke within 7 days of onset and are aged between 35 and 75 years;(4) NIHSS score ≥ 3 and ≤ 20, with no physical disability related to the study prior to disease onset;(5) Clear consciousness, defined as GCS score ≥ 13 points;(6) Individuals who voluntarily participate in this study and provide informed consent form.

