Point Selection and Positioning: The DU meridian Baihui (DU20), Dazhui (DU14; Figure 2), and temporal three-needle are selected based on acupuncture and moxibustion (17) and Jin’s Three Needle Therapy (18). Baihui (DU20) acupoint positioning: Located 5 inches above the center of the head at the current hairline, or at the midpoint of the line connecting the tips of both ears. Dazhui (DU14) acupoint positioning: Located on the posterior midline, in the depression below the 7th cervical spinous process. Positioning of temporal three-needle: Temporal I needle: Located 2 inches above the hairline at the ear tip. Temporal II needle: 1 inch forward and laterally from Temporal I needle. Temporal III needle: 1 inch backward and laterally from Temporal I needle (Figure 3). Needles: Acupuncture needles, 1-inch in length, produced by Suzhou Tianxie Acupuncture Instrument Co., Ltd. (Production lot number: SuμRegistration 20,162,200,894)Attention: After acupuncture treatment, patients should apply pressure to the needle site to prevent subcutaneous bleeding and cleanliness. During the treatment period, patients should avoid consuming raw and cold fruits, shrimp, beef, mutton, and other similar foods.Course of Electroacupuncture: Needles will be retained for 30 min per session, once daily, for a continuous duration of 10 days.The acupuncture points of Du-14 (Dazhui), Du-20 (Baihui), and the temporal three-needle points will be connected to the positive and negative terminals of the G6805 electroacupuncture device (Qingdao Xinsheng Industrial Co., Ltd.). A dispersive-dense wave will be selected, with a frequency of 50 Hz and an intensity of 1 mA, and electroacupuncture treatment will be performed for 30 min. No manual needle manipulation will be performed during needle retention to eliminate inter-practitioner variability.

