In pain management, its mechanisms are focused on peripheral and central pathways, including reducing pain transmission and enhancing the release of endogenous opioids. In the fields of cancer pain, neurological diseases, and post-stroke recovery, acupuncture demonstrates increasing therapeutic advantages, not only improving the quality of life for patients but also offering more treatment options. However, the clinical application of acupuncture still faces many challenges, including the need for more clinical studies to further validate its efficacy and mechanisms.

The aim of this study is to determine whether acupuncture could improve vascular function in patients with AIS, thereby reducing NIHSS scores and preventing further disease progression. In this randomized controlled trial, we aim to improve patients’ neurological function and daily living abilities through acupuncture. To achieve this, we selected a series of scales and outcomes to comprehensively assess the efficacy of acupuncture. To objectively assess stroke severity, we selected the NIHSS as the primary outcome, a scale that comprehensively evaluates patients’ stroke conditions. To assess the quality of daily life, we employee the Modified Barthel Index (MBI) and the Modified Rankin Scale (mRS) as secondary outcomes.

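### The 1- and 3-month mRS and MBI visits are counted from discharge, so a difference in length of stay between arms would become a difference in assessment time

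*Protocol article*

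**What the plan says.** The Follow-up section of the protocol article sets the longer-term visits: "Patients will be followed up at 1 and 3 months post-discharge". The instruments to be used at those two visits are the MBI and the mRS. The Discussion gives both scales their status: "we employee the Modified Barthel Index (MBI) and the Modified Rankin Scale (mRS) as secondary outcomes".

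The in-hospital schedule uses another time origin. Under Outcome measurement, "NIHSS scores will be assessed once before treatment (Day 1), during treatment (Day 5), and after treatment (Day 10"). For the functional scales, the same section has this schedule: "BMI and mRS scores will be assessed before treatment (Day 1) and after treatment (Day 10"). I take BMI there as a slip for MBI. The blood indices follow the same Day 1, 5 and 10 calendar (Blood serum index).

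On setting, the Study design section says "A total of 66 emergency inpatients will participate in this study", so participants are in hospital when randomised and leave afterwards. The article gives no length of stay, no discharge day and no link between discharge and Day 10. The reference to preset time points under Data monitoring and statistical analysis gives the follow-up visits no other origin.

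**The concern.** mRS and MBI measure recovery, and recovery depends on how much time has passed. A fair comparison needs both arms to be scored at the same time after a common starting point. Randomisation supplies that point. Discharge does not, because it happens later and can depend on the arm.

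The article leaves two routes open for such dependence. Under Random allocation, the attending physicians hold the allocation envelopes and act on them. The Blinding section covers laboratory staff, outcome assessors and statisticians, but says nothing about whoever decides discharge. Also, the trial's own hypothesis is that acupuncture improves neurological function and daily living ability, and that could itself change the length of stay.

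At stake is the comparison of mRS and MBI at the only two visits beyond Day 10. Any difference in mean stay passes day for day into a difference in mean assessment time, and randomisation cannot balance it because it arises afterwards.

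**Working it through.** The document gives no figure for visit timing relative to randomisation, so there is none to reproduce. The sample size rests on NIHSS and is not touched by this point.

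**Inputs**
- From the Follow-up section: visits at discharge plus 1 month and plus 3 months, taken here as 30 and 90 days.
- From the Outcome measurement section: Day 1 is the assessment before treatment. I treat randomisation and Day 1 as the same origin.
- Assumed: length of stay L, counted from randomisation to discharge. I use 14 days as the reference and 10 and 28 days as a range.
- Assumed: difference in mean stay between arms, d = 3 to 5 days.

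**Formulas**
- Time from randomisation to visit = L + 30 or L + 90.
- Between-arm difference in visit time = d, at both visits.
- Relative shift = d / (L + 30) or d / (L + 90).

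**Results**

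| Assumed stay L | 1-month visit at day | Shift, d = 3 to 5 | 3-month visit at day | Shift, d = 3 to 5 |
|---|---|---|---|---|
| 10 | 40 | 3/40 to 5/40 = 7.5 to 12.5% | 100 | 3/100 to 5/100 = 3 to 5% |
| 14 | 44 | 3/44 to 5/44 = 6.8 to 11.4% | 104 | 3/104 to 5/104 = 2.9 to 4.8% |
| 28 | 58 | 3/58 to 5/58 = 5.2 to 8.6% | 118 | 3/118 to 5/118 = 2.5 to 4.2% |

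For a wider range of d at L = 14: 2 days gives 2/44 = 4.5% and 2/104 = 1.9%; 10 days gives 10/44 = 22.7% and 10/104 = 9.6%.

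The base must be L + 30 or L + 90. Dividing by 30 or 90 alone measures the shift against time since discharge, which is not the time over which recovery accrues, and overstates it.

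**Direction.** While patients are still improving, a shorter stay in the acupuncture arm means earlier scoring, which would tend to work against acupuncture. A longer stay would tend to favour it. The document does not say which is likelier.

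**With visits counted from Day 1,** both fall at the same time in each arm whatever L is, so the difference due to length of stay is 0 by design.

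**The case against.** The strongest reply is that both arms share a 10-day calendar. Acupuncture is given "once daily, for a continuous duration of 10 days", and under Interventions the control group's medication also runs for 10 days. Scores and blood samples are taken in both arms through Day 10. That makes a large difference in stay less likely, and if every patient left when the course ended the problem would vanish. This stands as a limit on the likely size. It does not settle the matter: the named control drugs are oral, and nothing ties discharge to Day 10.

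A reader might infer that the 10-day acupuncture course keeps that arm in hospital longer, or that the arms will in fact be seen at different times. With no length-of-stay data and a shared calendar, the document supports neither.

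A reader might also count the enrolment window ("Individuals experiencing their first stroke within 7 days of onset") as part of the bias. It is fixed before randomisation and balanced in expectation. It spreads visit times after stroke but does not separate the arms.

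Nor is it a bias between arms that patients with longer stays are scored later after stroke. That is variation between patients, and it affects the comparison only if stay differs by arm.

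Finally, visit windows and covariates are commonly left to a full protocol or SAP, so their absence is no fault. The time origin is different: the article states it outright.

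**Conclusion.** The point holds in conditional form and is minor. The discharge anchor allows the arms to be compared at different times after randomisation if length of stay differs, and nothing in the article excludes that. Neither the size nor the direction can be established from the document. The illustrative shift of about 7 to 11% at 1 month and 3 to 5% at 3 months rests on an assumed 14-day stay and an assumed 3 to 5 day difference. These are shifts in assessment time, not in mRS or MBI; the document gives nothing to convert one into the other.

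Only the post-discharge mRS and MBI are affected. The primary NIHSS at Days 1, 5 and 10 and the other Day 10 measures keep a common origin, so it would be wrong to read this as a threat to the primary result.

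**What to change.** In the Follow-up section, count both visits from randomisation (Day 1), at about Day 30 and Day 90, whatever the discharge date. In the results, report the time from stroke onset to each visit by arm, so that readers can see that the arms were assessed at comparable times.

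The cost is a change of wording and of the visit calendar; treatment and sample size do not change. The small downside is that a patient with a long stay may have the Day 30 assessment while still in hospital. Exact visit windows and a covariate for time from onset are optional and can be left to the full protocol or SAP.

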## Introduction

Stroke is currently recognized as the second leading cause of disability and mortality worldwide (1), with acute ischemic stroke accounting for approximately 85% of cases (2). In China, the incidence of stroke has been increasing annually over the past 30 years, making it the leading cause of death in the country (3). Stroke is characterized by high incidence rates, high recurrence rates, high disability rates, and high case fatality rates (4). Acute ischemic stroke (AIS) refers to a group of syndromes caused by various factors leading to impaired blood supply to brain tissue (5). This impairment triggers a series of cascade reactions, resulting in ischemic and hypoxic necrosis in the brain, as well as neurological deficits in clinical practice (6). The current preferred treatment methods include intravenous thrombolysis and intravascular intervention therapy (7). However, treatment for AIS is often delayed due to factors such as low public awareness, a narrow thrombolysis time window, and strict eligibility criteria for thrombolysis. Only 21.5% of AIS patients in China arrive at the emergency department within 3 h of onset, and 12.6% are eligible for thrombolysis treatment, with fewer than 3% actually receiving it. The average interval between patient arrival at the emergency department and the administration of thrombolytic drugs is 116 min, significantly longer than in developed countries (8). Very few patients in China receive timely and effective thrombolytic therapy within the designated time window; therefore, it is essential for these patients to seek alternative treatments. Acute cerebral infarction is classified as a type of “stroke” in traditional Chinese medicine. Acupuncture, an important adjunctive treatment during the acute phase of cerebral infarction (9), has been shown to promote collateral circulation and improve brain circulation and metabolism to some extent (10). Currently, some scholars recommend initiating acupuncture treatment as soon as the patient’s vital signs stabilize (11). Therefore, in the early stages of acute ischemic stroke, when thrombolysis is no longer feasible and medical conditions are underdeveloped, acupuncture may offer timely intervention to mitigate the extent of cerebral infarction, reduce sequelae, and decrease the likelihood of functional disability, thereby conserving social resources (12).

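### At the 1- and 3-month contacts the article names only MBI and mRS: recurrent stroke, death and open adverse events are not stated to be sought in both arms, and a late death could be analysed as a survivor's score

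*Protocol article*

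**What the plan says.** The Interventions section gives electroacupuncture "once daily, for a continuous duration of 10 days", and basic treatment in both groups also runs for 10 days.

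On monitoring, the Safety outcomes section states: "The researchers will closely monitor patients during treatment, recording vital signs such as temperature, respiratory rate, pulse rate, and blood pressure". On recording, it states: "Any adverse reactions from needling, including localized redness, swelling, pain, or other events, will be documented by the operator". It adds that the trial will use the "Common Terminology Criteria for Adverse Events (CTCAE) to categorize and grade the severity of adverse events". Neither of the last two sentences gives a start date, an end date or a restriction to one arm.

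The Follow-up section sets contacts at 1 and 3 months after discharge, "with assessments of daily living ability (using the MBI scale) and disability (using the mRS scale". It names nothing else for those contacts. The outcomes in the Abstract include neither recurrence nor death. Under Outcome measurement, the last NIHSS is on Day 10.

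Three other places bear on the point. The mRS criteria under Secondary results run from 0 to 5, with no grade for death. The Data monitoring and statistical analysis section fills missing values by LOCF, without limiting this to particular outcomes or reasons for missingness, and plans both ITT and PP analyses. The Termination criteria list deterioration needing intensive care and serious events as grounds for ending participation.

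The Introduction describes stroke by "high incidence rates, high recurrence rates, high disability rates, and high case fatality rates". The Discussion gives the aim as improving vascular function, "thereby reducing NIHSS scores and preventing further disease progression".

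**The concern.** The trial sees its patients twice after treatment ends, yet the only stated content of those contacts is two functional scores. A recurrent stroke, a bleed, a readmission or an adverse event still open at Day 10 has no stated place on the form. The article itself presents recurrence and fatality as marks of the disease, and vascular protection as the mechanism under test.

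Three things are at stake:

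- **Lost events.** Events not asked about at 1 and 3 months may be impossible to recover when the data are analysed.
- **Interpretation.** A worse 3-month mRS cannot be separated into poor recovery from the index stroke and a new vascular event.
- **Deaths.** This is the sharpest point. With no mRS grade for death and a general carry-forward rule, the plan as stated would give a patient who has died the last score recorded in life.

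**Working it through.** **1. The plan's own figure.** The article gives no rate or count for recurrence, death or safety events. Its one relevant calculation is the sample size, which reproduces:

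- n = 2 × (1.96 + 1.28)² × 5.62² / (12.61 − 7.53)² = 2 × 10.4976 × 31.5844 / 25.8064 = 25.70, rounded up to 26 per group.
- Allowing for 20% dropout: 26 / 0.8 = 32.5, rounded up to 33 per arm, 66 in total.

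This rests on NIHSS alone. Counting events later does not change it.

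**2. What is stated, by period.**

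| Period | Stated collection |
|---|---|
| Days 1 to 10 | Close monitoring and vital signs; NIHSS on Days 1, 5 and 10; mRS on Days 1 and 10; blood markers |
| No period given | Needling reactions or other events, documented by the operator; CTCAE grading |
| No period beyond the study itself | Serious events and deterioration to intensive care, as grounds for termination |
| 1 and 3 months after discharge | MBI and mRS |

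The second and third rows might reach past Day 10. Neither tells a site to ask about events at the two later contacts. The person named as recorder in the second row is the operator, and only the acupuncture arm has a needling operator. No recorder is named for control patients.

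**3. Following one death through the stated rules.** Take a patient who dies between Day 10 and the 1-month contact.

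- No mRS grade from 0 to 5 describes death, so the 1- and 3-month values are missing.
- LOCF replaces a missing value with the last one observed, which is the Day 10 score.
- The patient then counts in the 3-month ITT comparison at the Day 10 level of disability.

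A death between the two contacts would carry the 1-month score forward in the same way. MBI behaves likewise, since its 0 to 100 range describes living patients.

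**4. How many patients this could touch.** The 3-month risks below are assumptions, because the documents give none. Expected events per arm = 33 × p. The chance of at least one event in the trial = 1 − (1 − p)^66.

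| Assumed risk p | Expected per arm | At least one among 66 |
|---|---|---|
| 1% | 0.3 | 48% |
| 2% | 0.7 | 74% |
| 5% | 1.7 | 97% |
| 10% | 3.3 | 99.9% |

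If p is read as the risk of death, the middle column is also the number of 3-month scores per arm that would be carried forward from life.

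**5. What counts by arm could show.** For 5% against 15% with 33 per arm and two-sided α = 0.05, the mean risk is 10%:

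- Standard error under no difference: √(2 × 0.10 × 0.90 / 33) = 0.0739.
- Standard error under the alternative: √((0.05 × 0.95 + 0.15 × 0.85) / 33) = 0.0728.
- Power = Φ[(0.10 − 1.96 × 0.0739) / 0.0728] = Φ(−0.61) = about 27%.

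Event counts would be descriptive only.

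**The case against.** The strongest reply is that this is silence, not error. The text is a journal article that condenses a fuller protocol, and the serious-event window, follow-up of open events and form content would normally sit there. The Follow-up section does not say that MBI and mRS are the only things recorded. The limit to the treatment period governs one sentence, on monitoring and vital signs, and the adverse-event and CTCAE sentences have no end date. The Termination criteria reach serious events over the study as a whole, and those reasons could be tabulated by arm. The passage on recurrence and fatality is background, and the progression aim is tied to NIHSS, measured to Day 10. A randomised comparison of 3-month mRS is also valid as a measure of total disability, whatever its cause.

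Much of this stands. A reader might infer that safety surveillance ends on Day 10, that recurrence and death are never counted by arm, or that control-arm events go unrecorded. The documents do not support any of these, for the reasons just given. Nor can one say there are no data on progression after Day 10, since mRS and MBI carry indirect information. One might also estimate what share of follow-up time lacks event capture, but that depends on a discharge day the article does not give. The two-sided 95% upper limit for 0 events in 33, 1 − 0.025^(1/33) = 10.6%, reflects the size of the arm and not the follow-up plan.

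Two things remain. Termination is a removal rule: it does not require asking about events at 1 and 3 months, and it may end contact with the patients whose later outcome matters most. And an mRS list without a death grade, combined with unrestricted LOCF, is stated text rather than omitted detail. The validity of the total-disability comparison depends on that point, because a carried-forward score does not measure the disability of a patient who has died.

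**Conclusion.** The point holds as a gap in what the later contacts are stated to collect, joined to a stated rule that handles death badly. Nothing in the article has recurrent stroke, death or open adverse events sought in both arms at 1 and 3 months, and a late death could be analysed as survival at the last recorded score.

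The size is modest: 0.3 to 3.3 patients per arm at assumed risks of 1% to 10%. At 2% or more, at least one event among 66 patients is more likely than not. The conclusion assumes that LOCF applies to the follow-up mRS and MBI, as its general wording suggests, and that no fuller protocol provides otherwise. The sample size and the primary NIHSS analysis to Day 10 are untouched. The change is still worth making now, because information not asked for at these contacts may not be obtainable later.

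**What to change.** - **Follow-up section.** Add to the existing 1- and 3-month contacts, in both arms: vital status, recurrent stroke with its date, bleeding, rehospitalisation, and the outcome of any adverse event open at Day 10.
- **Safety outcomes section.** State that serious events are collected up to the 3-month contact, and that recording applies to both arms.
- **Data monitoring and statistical analysis section.** Report these events as descriptive counts by randomised arm. State that no score from life is carried forward past a death, and say how deaths enter the 3-month mRS and MBI comparisons. One option is to treat death as a category below the worst living grade, which the Mann–Whitney test already named in the plan can accommodate.

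The cost is one more case report form page and a short amendment, with no extra visits, staff or procedures. The counts will be too small for a formal comparison and should be presented as such. If a fuller protocol already collects these items, a clarifying sentence is enough for that part, but the handling of deaths under LOCF still needs to be stated.
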